#### Follow-up and assessments

Follow-up visits will occur every 3 months, as outlined in Table 2, and will include clinical evaluation, imaging studies, laboratory testing, and assessment of adverse events. Imaging for tumor response assessment will be performed every 8 weeks from randomization until disease progression. The efficacy of YFXJD will be evaluated through progression-free survival, TCM symptom scores, activity levels, biochemical parameters, and exploratory biological indicators. Safety will be assessed according to protocol-defined criteria. The trial flowchart is presented in Figure 1.

**Table 2 tab2:** Schedule of trial.

Assessment/Time point	Screening	Baseline/Initiation	Treatment period	Treatment period	Long-term follow-up	End-of-treatment visit	Survival follow-up
	D -7	D0	D90 ± 7	D180 ± 7	D365 ± 7	Upon PD/Discontinuation	
Procedures							
Informed consent	✓						
Eligibility review	✓						
Data collection							
Demographic information	✓						
History of NSCLC & treatment	✓						
History of other diseases	✓						
Randomization & drug dispensing		✓	✓ (Re-supply)	✓ (Re-supply)			
Primary endpoints							
1. PFS (RECIST 1.1)			Imaging per protocol	Imaging per protocol	Imaging per protocol	✓ (Confirm PD)	Record death
2. TCM Syndrome Score	✓ (Baseline)		✓ (Interim)	✓ (Primary Time Point)			
Secondary endpoints (Efficacy)							
Tumor response (ORR/DCR)			✓	✓	✓	✓ (Final)	
Quality of life (EORTC QLQ)	✓ (Baseline)		✓	✓	✓		
Performance status (KPS)	✓ (Baseline)		✓	✓	✓		
Biomarkers							
Lymphocyte subsets	✓ (Baseline)		✓	✓	✓		
Inflammatory cytokines	✓ (Baseline)		✓	✓	✓		
Tumor markers	✓ (Baseline)		✓	✓	✓		
Safety assessments							
Clinical laboratory tests							
CBC, hepatic & renal function	✓	✓	✓	✓	✓	✓	
Urinalysis & stool routine	✓	✓	✓	✓	✓	✓	
AE/SAE collection	✓	✓	✓	✓	✓	✓	
EGFR-TKIs specific AE recording		✓	✓	✓	✓	✓	
Concomitant medication record		✓	✓	✓	✓		
Proportion with dose Mod./Disc.			Recorded	Recorded	Recorded	✓ (Final)	
Study administration							
Protocol deviation record		✓	✓	✓	✓		
CRF completion		✓	✓	✓	✓	✓	

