### Withdrawal/termination criteria

Participants will be withdrawn or terminated from the trial if any of the following conditions are met:Failure to adhere to the key procedures outlined in the study protocol, which may compromise the validity of the data obtained from that participant.The use of concomitant therapies that are prohibited by the protocol for the management of NSCLC or its symptoms.Discontinuation of osimertinib due to toxicity: Occurrence of severe adverse reactions attributable to osimertinib therapy that necessitate the permanent discontinuation of the targeted agent, as determined by the treating physician. This criterion focuses on adverse events (e.g., severe interstitial lung disease, hepatotoxicity, or intolerable grade 3/4 rash or diarrhea) that make continued osimertinib treatment unsafe.Withdrawal of consent: The participant voluntarily decides to withdraw from the study at any time for any reason.Loss to follow-up: The participant becomes unreachable or fails to attend scheduled study visits without providing reason, despite repeated attempts at contact by the research team.The principal investigator determines that continued participation is not in the best interest of the participant’s health and safety.

Participants who are discontinued from the study intervention will be encouraged to continue in the follow-up phase for the collection of survival and safety data, where feasible and with their consent. All reasons for withdrawal or discontinuation will be documented in the case report form.

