### Interventions

#### Osimertinib intervention

According to the CSCO Guidelines for the Diagnosis and Treatment of Non-Small Cell Lung Cancer (2024) and the FLAURA trial (13), the recommended first-line osimertinib regimen for advanced EGFR-mutant NSCLC is 80 mg orally once daily, which can be taken with or without food (14). Treatment will be continued until disease progression, unacceptable toxicity, or other discontinuation criteria are met.

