#### TCM intervention

The TCM intervention will be administered concurrently with EGFR-TKIs therapy and will continue until disease progression, unacceptable toxicity, or other criteria for treatment discontinuation are met. Both the YFXJD and placebo are manufactured as granules. Each sealed packet contains a fixed dose of granules (10 g per packet, 5:1 extraction ratio), with identical packaging to ensure complete blinding in terms of appearance, texture, smell, and taste. Matching placebo granules with similar appearance, odor, taste, and packaging, without active herbal ingredients. Are composed of pharmaceutical-grade excipients (primarily maltodextrin) with approved food colorants and flavorings.

Quality control of YFXJD granules includes: (1) botanical authentication of all raw herbs with voucher specimens deposited at the Shanghai University of TCM Herbarium; (2) compliance with Chinese Pharmacopoeia 2020 edition standards; (3) chemical fingerprinting by HPLC for batch-to-batch consistency; (4) 12-month stability testing; and (5) testing for pesticides, heavy metals, microbes, and adulterants. The YFXJD granules and placebo are produced under Good Manufacturing Practice (GMP) standards at Sichuan Neo-green Pharmaceutical Technology Development Co., Ltd. The manufacturer supplied the study products but had no role in study design, data collection, analysis, or manuscript preparation; no financial or non-financial competing interest exists.

Patients will be instructed to dissolve the contents of one packet in approximately 150–200 mL of hot water and to take it orally twice daily (morning and evening), 30 min after meals. The daily total dose will therefore consist of two packets. The dosage and administration frequency will remain constant throughout the treatment period unless modified due to tolerability issues as assessed by the investigator.

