##### Herb-drug interaction review

Osimertinib is primarily metabolized by hepatic CYP3A4. The following measures will be implemented: (1) systematic review of all herbal components for potential CYP3A4 interactions; (2) prohibition of concomitant herbal medicines known to interact with CYP3A4 (e.g., St. John’s Wort, Glycyrrhiza, Scutellaria); (3) specific monitoring for overlapping hepatic toxicity (ALT/AST every 4 weeks), gastrointestinal toxicity, and pulmonary toxicity (ILD monitoring); and (4) dose modification guidelines for osimertinib in case of grade ≥3 toxicity.

Participants who experience severe adverse events (AEs) assessed as related to the trial intervention will be provided with necessary post-trial medical care and may receive appropriate compensation in accordance with relevant regulations and the insurance protocol for this clinical trial. For any adverse reactions determined to be unrelated to the study medication, standard medical management will be provided based on a comprehensive assessment of the participant’s condition, including medical history, clinical symptoms, physical signs, and results from laboratory tests, imaging, and other diagnostic examinations.

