#### Secondary outcomes

Change in TCM Qi-Yin Deficiency Syndrome Score: The absolute change in the total score from baseline to 6 months (D180 ± 7), assessed using a pre-specified and validated TCM syndrome scale specific for Qi-Yin deficiency in lung cancer. The scale ranges from 0 to 48, with higher scores indicating more severe symptoms. The minimal clinically important difference (MCID) is 4 points. All TCM assessors will undergo a 2-day training session with standardized patients, and inter-rater reliability (kappa ≥ 0.80) will be established prior to study initiation.Objective Response Rate (ORR) and Disease Control Rate (DCR) as per RECIST 1.1 (15).Duration of Response (DOR).Overall Survival (OS).Change in health-related quality of life assessed using the European Organization for Research and Treatment of Cancer Quality of Life Questionnaire Core 30 (EORTC QLQ-C30) (16) and its lung cancer-specific module (QLQ-LC13) (17).Change in Karnofsky Performance Status (KPS) score (18).Incidence, type, severity, and relationship to study treatment of all Adverse Events (AEs) and Serious Adverse Events (SAEs), graded according to the National Cancer Institute Common Terminology Criteria for Adverse Events (NCI CTCAE) Version 5.0 (19).

Evaluation of EGFR-TKIs-related specific adverse reactions:Rash: A validated skin toxicity assessment tool (e.g., HFSR-14 scale or specialized assessment based on CTCAE v5.0 dermatology criteria) will be used to record the incidence, maximum severity (grade), time to onset, duration, and management measures (e.g., topical/systemic medications, dose modifications) of rash.Diarrhea: The incidence, maximum severity (graded per CTCAE v5.0 gastrointestinal criteria), duration, frequency of diarrhea will be recorded, along with the proportion of patients requiring EGFR-TKIs dose modification, interruption, or discontinuation due to diarrhea. The use of anti-diarrheal medications will also be documented.The proportion of patients requiring EGFR-TKIs dose reduction, interruption, or permanent discontinuation due to the above or any other AEs.Changes in serum levels of inflammatory cytokines (IL-2, IL-6, IL-10, TNF-*α*, IFN-*γ*).Changes in peripheral blood lymphocyte subsets (CD3^+^, CD4^+^, CD8^+^, CD4^+^/CD8^+^ ratio, NK cells).Changes in serum tumor marker levels (CEA, CYFRA21-1, SCC-Ag, NSE).

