### Sample size

The sample size for this study was calculated based on the primary outcome of progression-free survival (PFS). Based on the FLAURA trial, the median PFS for osimertinib monotherapy is approximately 18.9 months. To achieve 80% power at a two-sided significance level of α = 0.05 for detecting a clinically meaningful difference, a target hazard ratio (HR) of 0.66 was assumed, corresponding to a median PFS of approximately 28.6 months in the experimental group (an absolute extension of 9.7 months). This effect size is consistent with the HR observed in the CATLA trial (HR 0.68).

Using the Schoenfeld formula for the log-rank test, the required number of PFS events (d) is calculated as:
$$d=4\times {\left(Z\_(1-\alpha /2)+Z\_(1-\beta )\right)}^{2}/{\left(\ln\;\mathrm{HR}\right)}^{2}$$

With α = 0.05 (two-sided), β = 0.20 (power = 0.80), Z_(1-α/2) = 1.96, Z_(1-β) = 0.84, and HR = 0.66:
$$d=4\times {\left(1.96+0.84\right)}^{2}/{\left(\ln\;0.66\right)}^{2}\approx 176\;\text{events}$$

Under a 1:1 randomization ratio with an accrual period of 12 months, a minimum follow-up of 12 months, and an expected event rate of approximately 65% at the end of follow-up, the required total sample size is approximately 270 patients (135 per group). Accounting for an estimated dropout rate of approximately 20%, we plan to enroll 200 patients (100 per group) to ensure that sufficient patients complete the primary endpoint assessment. The planned enrollment of 200 patients is expected to yield approximately 130 PFS events, providing approximately 75% power at the planned analysis. An interim analysis for futility is planned after 50% of the expected PFS events have been observed, with the option to increase sample size if warranted by conditional power calculations.

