#### Comparative analyses

Between-group comparisons of continuous variables will use the independent samples t-test or Mann–Whitney U test, as appropriate. Categorical variables will be compared using the Chi-square test or Fisher’s exact test. For repeated measures (TCM syndrome score, QoL), baseline-adjusted mixed models for repeated measures (MMRM) will be used, with treatment group, visit, treatment-by-visit interaction, and baseline value as fixed effects, and participant as random effect.

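### If YFXJD prolongs PFS as assumed, crude adverse-event percentages modestly overstate its common, steadily accruing harms; add a time-to-first-event comparison beside them.

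*Protocol article*

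**What the plan says.** The Secondary outcomes section makes the incidence of AEs and SAEs an outcome, and for diarrhea states: "The incidence, maximum severity (graded per CTCAE v5.0 gastrointestinal criteria), duration, frequency of diarrhea will be recorded". Descriptive statistics reports categorical data as counts and percentages. Comparative analyses then says: "Categorical variables will be compared using the Chi-square test or Fisher’s exact test". That sentence does not name adverse events, but no other stated between-arm test covers their incidence. Survival analysis applies Kaplan–Meier, log-rank and Cox methods to PFS and OS only.

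On how long patients are observed:

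- **Osimertinib intervention:** "Treatment will be continued until disease progression, unacceptable toxicity, or other discontinuation criteria are met".
- **TCM intervention:** YFXJD or placebo "will continue until disease progression, unacceptable toxicity, or other criteria for treatment discontinuation are met".
- **Table 2 (Follow-up and assessments):** the AE/SAE row is ticked up to the end-of-treatment visit, timed "Upon PD/Discontinuation", and is blank under survival follow-up.
- **Withdrawal/termination criteria:** patients who stop the intervention "will be encouraged to continue in the follow-up phase for the collection of survival and safety data, where feasible and with their consent".

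On the expected effect, the Sample size section states: "a target hazard ratio (HR) of 0.66 was assumed, corresponding to a median PFS of approximately 28.6 months in the experimental group".

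**The concern.** A crude percentage compares arms fairly on AE hazard only if they are watched for similar lengths of time. Here observation for harms normally ends at progression. If the trial succeeds, the YFXJD arm is watched longer and collects more first events even when the herb adds no risk. The percentage then mixes hazard with exposure.

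Two readings are at stake. A small excess under YFXJD could be taken for toxicity when it is only longer treatment. A true reduction in toxicity could be partly masked. The second matters because the Introduction mentions early signs of lower toxicity and the Objectives promise a systematic assessment of adverse events.

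**Working it through.** **Inputs from the Sample size section.** Control median PFS 18.9 months; PFS hazard ratio 0.66; accrual 12 months and minimum follow-up 12 months, so 12 to 24 months per patient; 100 per arm; 20% dropout.

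**Assumptions not in the protocol.** Exponential PFS; uniform accrual; dropout exponential, reaching 20% by 18 months; constant AE hazard *h*, equal in both arms unless stated. No AE rates are given, so *h* is varied. Hazards of 0.02, 0.05 and 0.10 per month correspond to 12-month risks of 1 − exp(−12*h*) = 21%, 45% and 70%.

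**Step 1: the plan's own figure.** 18.9 / 0.66 = 28.6 months, as stated. Monthly progression hazards are λ = ln 2 / 18.9 = 0.0367 (control) and 0.66 × 0.0367 = 0.0242 (YFXJD). The dropout hazard is δ = −ln(0.8)/18 = 0.0124.

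**Step 2: mean time under AE observation.** This is the average of [1 − exp(−(λ+δ)u)]/(λ+δ) over u from 12 to 24 months.

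- Without dropout (δ = 0): 13.06 v 14.50 months, ratio 1.11.
- With dropout: 11.83 v 13.07 months, ratio 1.10.

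**Step 3: crude incidence at equal hazard.** This is the average over the same u of *h*/(*h*+λ+δ) × [1 − exp(−(*h*+λ+δ)u)].

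Worked case, *h* = 0.05. In the control arm the total hazard is 0.0991, the first factor is 0.505 and the averaged bracket is 0.822, giving 41.5%. In the YFXJD arm these are 0.0866, 0.577 and 0.780, giving 45.0%.

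| *h* per month | Control | YFXJD | Gap (points, unrounded inputs) |
|---|---|---|---|
| 0.002 | 2.3% | 2.6% | 0.2 |
| 0.02 | 20.4% | 22.3% | 2.0 |
| 0.05 | 41.5% | 45.0% | 3.6 |
| 0.10 | 61.9% | 66.2% | 4.4 |

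If half the patients stay under AE follow-up after progression at the same hazard, the last two gaps fall to 1.8 and 2.2 points. With complete follow-up they vanish.

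**Step 4: false rejection with no true difference in AE hazard.** Simulation of 10,000 trials, 100 per arm, two-sided 0.05, PFS hazard ratio 0.66 and 20% dropout unless stated.

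| Scenario | Chi-square | Log-rank |
|---|---|---|
| *h* = 0.05 | 8.3% | 5.0% |
| *h* = 0.10 | 9.9% | 5.8% |
| *h* = 0.05, no dropout | 9.2% | 4.7% |
| *h* = 0.10, no dropout | 11.9% | 5.1% |
| *h* = 0.05, half followed after progression | 6.0% | 4.7% |
| *h* = 0.10, half followed after progression | 6.5% | 5.3% |
| *h* = 0.02 | 6.2% | 5.1% |
| Early onset (50% susceptible, 1 per month) | 5.6% | 5.1% |
| Rare event, *h* = 0.002 | 4.7% | 4.0% |
| PFS hazard ratio 1, *h* = 0.05 | 5.0% | 4.7% |

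Fisher's test, in a separate run of 5,000 trials, rejects in 6.7% (*h* = 0.05) and 7.5% (*h* = 0.10). In that run the Cox hazard ratio averages 1.00, with 95% interval coverage of 95.0% and 94.8%. If AE and progression risks share a gamma frailty of variance 0.5, chi-square rejects in 7.8% and 8.5%, log-rank in 5.5% and 5.3%, and the mean hazard ratio is 1.03 and 1.02.

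**Step 5: power when AE hazards truly differ (20% dropout).**

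| AE hazard ratio, *h* | PFS hazard ratio | Chi-square | Log-rank |
|---|---|---|---|
| 0.6, 0.05 | 0.66 | 33% | 57% |
| 0.6, 0.10 | 0.66 | 37% | 76% |
| 0.6, 0.05 | 1 | 48% | 56% |
| 0.6, 0.10 | 1 | 59% | 75% |
| 1.5, 0.05 | 0.66 | 64% | 52% |
| 1.5, 0.05 | 1 | 41% | 50% |

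**The case against.** The strongest reply is that this is ordinary analysis-plan content. The article does not name a test for adverse events, nothing in it rules out exposure adjustment, and the unseen plan may provide it. A percentage with a chi-square or Fisher test also answers the incidence outcome as worded. Both points limit the weight of the finding. It stands because the article does fix a general rule, and that rule suits this design less well than a simple alternative.

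Other points also carry weight:

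- **Status of the p-values.** Additional analyses sets the 0.05 level for the primary endpoint and treats exploratory secondary results as hypothesis-generating. If that covers adverse events, the rejection rates above show how often the comparison would mislead a reader; they are not formal error rates.
- **AE rates are assumed.** The larger gaps need 12-month risks of 45-70% accruing steadily. With 100 per arm, the 95% interval for a difference at these rates is about ±13 to 14 points, so the largest gap is about a third of its half-width.
- **Diarrhea may start early.** If so, it is little affected.
- **Accrual.** Trial status reports 38 patients by July 2026. If the other 162 enrol by December, mean follow-up is about 15.9 months and the gaps are 3.1 and 4.0 points. Conversely, following until the stated 130 events would need about 29 months' minimum follow-up under exponential PFS. Without dropout, that raises the exposure ratio to 1.20 and the gaps to 2.9-7.6 points for 12-month risks of 10-60%.
- **Direction.** The spurious excess counts against YFXJD, so it does not falsely reassure. The time-based comparison also detects a true harm less often when PFS improves (52% v 64%). Part of that 64% is exposure bias, since the order reverses when PFS is equal (50% v 41%). This is a reason to show both.

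**Conclusion.** The concern holds as a minor, optional improvement. If YFXJD delivers the assumed PFS benefit, and a harm is common and accrues steadily, the crude comparison shows an excess of about 2 to 4 points that is only longer observation, and it loses much of its ability to show a true reduction. This rests on assumed AE hazards, exponential PFS, AE recording that largely stops at progression, and the target hazard ratio of 0.66. The distortion is absent if PFS does not differ, is slight or absent for early rash and for rare events such as ILD, and is about halved if half the patients remain under safety follow-up after progression. Confidence is medium, mainly because the protocol gives no AE rates.

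**What to change.** Keep the crude percentages. Under Comparative analyses or Survival analysis, add one comparison for common treatment-emergent harms that can begin at any point on treatment, such as hepatic toxicity and diarrhea:

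- time from first dose to first event, with observation ending at the end of treatment, reported as a cause-specific hazard ratio with 95% CI;
- cumulative incidence shown descriptively, with progression or death as competing events;
- analysis in the treated set defined under Safety population. The Statistical analysis section currently puts safety on the ITT set, and the treated set is defined without being assigned to any analysis.

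Report onset and duration among affected patients descriptively. Rash and rare events such as ILD can stay as percentages.

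The cost is a few sentences and a few tables, using first-event dates from routine AE records, with no added visits or tests.

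### The repeated-measures model names only a participant random effect as its within-patient term; fitted literally, this forces equal variance at all visits and can miscalibrate the D180 standard error

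*Protocol article*

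**What the plan says.** The protocol article, Comparative analyses, states: "For repeated measures (TCM syndrome score, QoL), baseline-adjusted mixed models for repeated measures (MMRM) will be used". The sentence continues by listing the model's terms: "with treatment group, visit, treatment-by-visit interaction, and baseline value as fixed effects, and participant as random effect". The only within-patient term in that list is the last one, "and participant as random effect". It mentions no residual covariance structure, no fallback structure and no robust standard error.

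Under Secondary outcomes the TCM endpoint is tied to one visit: "The absolute change in the total score from baseline to 6 months (D180 ± 7", and of the scale it says: "The scale ranges from 0 to 48, with higher scores indicating more severe symptoms". Table 2 (Follow-up and assessments) schedules the TCM score at baseline, D90 and D180, and marks D180 as "Primary Time Point". The Table 2 row that begins "Quality of life (EORTC QLQ" has three post-baseline assessments: D90, D180 and D365.

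The article gives no standard deviation by visit and no within-patient correlation for either outcome.

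**The concern.** The sentence joins two things that do not sit easily together. The label MMRM usually denotes a model whose within-patient covariance is set through the residuals, often unstructured. A participant random effect, coded as written, is a random intercept with independent residuals of equal variance. That is compound symmetry: the same variance at every visit and the same correlation between every pair of visits.

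The TCM endpoint is a contrast at a single visit. Under compound symmetry its standard error is computed from a variance pooled over all visits rather than from the spread at D180. If the spread at D180 is larger than at D90, the confidence interval and p-value for the D180 difference are too optimistic; if it is smaller, they are too conservative. Patients enter with a diagnosed syndrome and may then improve, plateau or progress, so a change in spread is plausible, but the article gives no data either way.

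**Working it through.** **Inputs from the article.** Post-baseline visits: two for the TCM score and three for quality of life (Table 2). Sample size, from Sample size: "we plan to enroll 200 patients (100 per group". Dropout of about 20% (Sample size). Nominal two-sided level 0.05, which the article states for the primary endpoint and which is used here as the reference level. There is no planned figure for this model to reproduce.

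**Assumed inputs.** The SDs by visit (s90, s180), the within-patient correlation (0.5) and, in the simulation, the missingness pattern. SDs are around the fixed effects.

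**Step 1: what the literal model implies.** With a random intercept of variance a and independent residuals of variance e, every visit has variance a + e and every pair of visits has correlation a/(a + e).

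**Step 2: what is restricted.** An unstructured covariance has k(k+1)/2 parameters for k visits: 3 for k = 2 and 6 for k = 3. The random-intercept model has 2. For the TCM score there is a single correlation, which is free apart from being non-negative, so the one real restriction is s90 = s180. For quality of life, both equal variances and equal correlations are imposed.

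**Step 3: effect on the D180 standard error.** With complete data and a group-by-visit term, the D180 estimate is essentially the baseline-adjusted group difference at D180 under either structure. Its true SE is s180 × √(2/100). The literal model reports √((s90² + s180²)/2) × √(2/100). The sample size cancels:

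R = model SE / true SE = √((s90² + s180²)/2) / s180

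Actual level of a nominal 5% test = 2 × (1 − Φ(1.96 × R))

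**Step 4: numbers for the TCM score.**

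- SD 6 then 8: R = √50 / 8 = 0.884. SE 12% too small, actual level 8.3%.
- SD 6 then 7: R = √42.5 / 7 = 0.931. SE 7% too small, actual level 6.8%.
- SD 8 then 6: R = √50 / 6 = 1.179. SE 18% too large, actual level 2.1%.

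Over a range of ratios:

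| s180 / s90 (assumed) | R | Actual level |
|---|---|---|
| 0.8 | 1.13 | 2.7% |
| 1.0 | 1.00 | 5.0% |
| 1.15 | 0.94 | 6.6% |
| 1.25 | 0.91 | 7.6% |
| 1.5 | 0.85 | 9.6% |
| 2.0 | 0.79 | 12.1% |

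**Step 5: simulation with missing data.** 3000 runs, 100 per arm, D90 and D180, baseline-adjusted, correlation 0.5, 20% of D180 values missing independently of the scores.

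| s180 / s90 | Literal model: model SE vs empirical SE | Level | Unstructured: model SE vs empirical SE | Level |
|---|---|---|---|---|
| 1.0 | 0.154 vs 0.156 | 5.3% | 0.154 vs 0.156 | 5.2% |
| 1.25 | 0.172 vs 0.195 | 8.5% | 0.193 vs 0.195 | 5.7% |
| 1.5 | 0.193 vs 0.234 | 10.6% | 0.232 vs 0.234 | 4.8% |

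The Monte Carlo error of a 5% rate is √(0.05 × 0.95 / 3000), about 0.4 percentage points. The unstructured model brings the level back to about 5%. The empirical SEs of the two models agree closely, so the change costs almost no precision.

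**Step 6: quality of life at D180, three visits.** The same formula with the mean of three variances gives:

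- SDs 1 / 1.25 / 1.5: R = 1.01, level 4.7%.
- SDs 1 / 1 / 1.5: R = 1.19, level 2.0%.
- SDs 1 / 1.25 / 1: R = 0.87, level 8.8%.

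A steady rise in spread therefore leaves the D180 contrast almost right, while other patterns do not.

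**The case against.** The strongest reply is that the article does not say the residuals are independent or of equal variance. Naming the participant as a random effect is common loose wording for the subject unit, MMRM normally implies a structured residual covariance, and covariance type and degrees of freedom are details that an article leaves to the SAP, which is not shown. Much of this stands: that the random effect is the whole within-patient model is an inference from the wording. But the sentence is not silent. It lists the model's terms and names one within-patient term, and a programmer who follows it gets compound symmetry.

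The second reply is that the harm depends on SDs the article does not give. That also stands. The SDs above are assumptions, and at equal SDs there is no error.

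The third is that the outcomes are secondary and that the article treats exploratory secondary results as hypothesis-generating. This limits the importance of the point, but a miscalibrated confidence interval is still worth avoiding when the remedy is one sentence. (Table 2 groups the TCM score with the primary endpoints, unlike the Abstract and the Outcomes section; that is a separate inconsistency and the point does not rest on it.)

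A reader might infer three stronger things that the documents do not support:

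- That equal correlations or uneven visit spacing harm the TCM analysis. The TCM score is scheduled at baseline, D90 and D180: evenly spaced, with one post-baseline correlation and no D365 assessment. Those arguments reach only quality of life.
- That the D180 result will be anti-conservative. The direction is unknown.
- That the treatment estimate is biased when dropout depends on earlier scores. Handling of missing data plans multiple imputation for continuous variables. If the model is fitted to completed data, such bias would come from the imputation model rather than from the random effect, and nothing here quantifies it.

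**Conclusion.** The point holds as a minor defect of specification. Taken literally, the stated model fixes a common variance across visits, and for quality of life a common correlation too. For the TCM score only the equal-variance restriction matters. For assumed SD ratios from 0.8 to 2.0, the actual level of a nominal 5% test at D180 runs from 2.7% to 12.1%, and is 5.0% when the SDs are equal. These figures rest on the random-intercept reading, on assumed SDs and on complete data; the simulation with 20% of D180 values missing gives slightly larger errors at ratios of 1.25 and 1.5. The article does not allow the actual size or direction to be determined. The PFS analysis is not touched.

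**What to change.** In Comparative analyses, delete the participant random effect and specify an unstructured within-participant covariance across visits, fitted by REML with Kenward-Roger degrees of freedom. Name a fallback in case it does not converge; heterogeneous compound symmetry, for example, would still let the variances differ. The unstructured covariance should replace the random effect rather than be added to it, because the two together are over-parameterised. If the SAP already specifies this, confirm it and correct the sentence.

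The statistical cost is 3 covariance parameters for the TCM score and 6 for quality of life, against 2 under the literal model: 1 and 4 extra, which is small for 200 patients. A baseline-by-visit interaction is an optional refinement that this point does not require. In practice the change is one sentence and one line of SAS code, with no new data. Database lock is planned for Q1 2028 (Trial status), so it can be made well before unblinding; if handled as a protocol amendment, it needs the ethics committee approval described under Ethics and dissemination.
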